### Exposure

A number of statin users will have only one prescription before stopping. Because they did not receive a repeat prescription, it cannot be certain that these patients actually ever took statins. So, for the main analysis, having excluded patients with one prescription, we will run a sensitivity analysis including all patients with one or more prescriptions. We will report on the percentage of patients that had only one prescription and describe characteristics of this group.

The following statins will be included into the analysis: atorvastatin, simvastatin, fluvastatin, pravastatin and rosuvastatin. As the statin most commonly prescribed in the overall study period, simvastatin—used by around 70% of patients—will be used as the reference drug.

### Outcome

The outcome will be defined as a discontinuation of statin use if there are no prescriptions within the 90 days following the expected finishing date of a prescription. The first such event will be considered as an outcome, and further prescriptions will not be used in the analysis of discontinuation. A 90-day exposure window has been used in other CPRD studies^29^
^30^ because it is the longest prescription length that can be issued in the UK. The date of the outcome will be defined as the expected finishing date of the prescription.

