### Sample selection

This will be a prospective open cohort study of new statin users identified during the study period between 1 January 2002 and 30 September 2013. Incident cases who discontinued statin therapy will be identified during follow-up. Patients will enter the cohort on the date of their first recorded statin prescription within the study inclusion period. Patients will be followed up until the earliest of: death; deregistration with the practice; last upload of computerised data; 1 year from the date the study inclusion period ended. Patients will be subdivided into two groups evaluated on the date when they started taking statins: those without CVD records before the entry date (taking statins for primary prevention); those with CVD diagnosed at or before entering the study (taking statins for secondary prevention). Patients without CVD at the baseline date will be followed up until the time of a CVD diagnosis if it occurs before the study exit date.

We expect the rate of discontinuation to be lower in the secondary prevention group, and this subdivision will make our results more easily comparable with existing studies.

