### Additional analyses

Patients might discontinue statins within the first year or after a longer period. The characteristics of these patients might differ, so we shall rerun the main analysis twice, in the first censoring all patients who did not discontinue before the end of year one, and in the second removing all patients who did discontinue before the end of year 1.

Some statin users have discontinuous use, with one or more restarts against a background of fairly continual usage. We shall define a subcohort in the study period for patients who discontinued statins (the outcome date in the main analysis will be their new entry date) and follow them until they have a new statin prescription or they are censored as described in the Study design section. We shall describe how many people restarted statin therapy within the first 6 months, 7–12 months and 12 or more months after their new entry dates using Kaplan-Meier estimates. We shall report descriptive statistics for the covariates listed above both for stoppers who restarted and those who did not.

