### Sensitivity analyses

Apart from the two sensitivity analyses already mentioned relating to exposure and missing values, two others will be included. One will be to facilitate comparison with the results of the Zhang *et al*^27^ study for long-term statin discontinuation. In this, we will define an outcome as an absence of any statin prescriptions within the 12 months (365 days) following the expected finishing date of a prescription. As before, the expected last date will also be the date of the outcome. Because of the longer period required for an outcome, for this analysis, we will remove patients with less than 2 years of follow-up records. The other will be run to investigate the influence of possible changes in baseline variables over the full study period, by rerunning the analysis with the follow-up period restricted to 5 years.

A 1% level of statistical significance will be used to allow for multiple comparisons. Stata V.13 will be used for all the analyses.

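### Discontinuation needs 90 (or 365) observed prescription-free days, but time at risk runs to exit, so rates are biased wherever prescriptions cannot be seen beyond exit

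*Protocol article*

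**What the plan says.** - **Event** (Outcome): a stop is declared "if there are no prescriptions within the 90 days following the expected finishing date of a prescription". Its date lies at the start of that window: "The date of the outcome will be defined as the expected finishing date of the prescription".
- **Exit** (Sample selection): "Patients will be followed up until the earliest of: death; deregistration with the practice; last upload of computerised data", or one year after inclusion closes. Inclusion covers the "study period between 1 January 2002 and 30 September 2013", so the latest exit is 30 September 2014. There is one further exit: "Patients without CVD at the baseline date will be followed up until the time of a CVD diagnosis", if that comes first.
- **Rates** (Statistical analysis): stoppers divided by person-years, overall and by calendar year, among other breakdowns.
- **Long-gap version** (Sensitivity analyses): the outcome becomes an "absence of any statin prescriptions within the 12 months (365 days) following the expected finishing date of a prescription", again back-dated, and patients with under two years of follow-up are dropped.
- **Restart subcohort** (Additional analyses): "the outcome date in the main analysis will be their new entry date".

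No section ends time at risk before exit, or says how a supply that runs out less than 90 (365) days before exit is classified.

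**The concern.** The event is dated at one point and can be verified only 90 or 365 days later. If a patient's record ends at exit, there are two ways to apply the rules, and both go wrong:

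- **Require the full window.** The last 90 (365) days before exit add person-time but can never add an event, so rates are too low.
- **Accept a truncated window as prescription-free.** A continuing user whose supply lapsed days before death or a move is recorded as a stopper, so rates are too high near exit.

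Stopping rates, and whether they have changed over time, are stated aims. The distortion grows as follow-up shortens. It therefore falls most heavily on the last calendar year, on groups with high mortality or turnover, and on the 365-day analysis. The minimum follow-up rules (one year in the main analysis, two in the long-gap analysis) guarantee some verifiable time but leave the end of follow-up untouched.

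**Working it through.** The plan gives no figure on this point to reproduce. Its sample-size figures (5362 and 1196) are unaffected.

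**Inputs.** From the article: W = 90 or 365 days, exit rules, minimum follow-up of 1 or 2 years, last exit 30 September 2014. Assumed, because the article gives no cohort rate: a constant stopping hazard h of 0.05 to 0.7 per year. The top of that range reflects the 49% one-year adherence cited in the Introduction: −ln(0.49) = 0.71.

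**Step 1: closed form, full window required, record ending at exit time T.**

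- Events per patient: E = 1 − exp(−h(T − W))
- Person-years per patient: P = E/h + exp(−h(T − W)) × W
- Estimated/true rate: (E/P)/h

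Example, h = 0.2, T = 2, W = 90/365.25 = 0.246: E = 1 − exp(−0.351) = 0.296; P = 1.479 + 0.704 × 0.246 = 1.653; ratio = (0.296/1.653)/0.2 = 0.895.

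| Follow-up T | 90-day ratio, h = 0.05 to 0.7 | 365-day ratio, h = 0.05 to 0.7 |
|---|---|---|
| 1 year | 0.76-0.80 | not eligible |
| 2 years | 0.88-0.93 | 0.51-0.59 |
| 3 years | 0.92-0.97 | 0.68-0.81 |
| 5 years | 0.96-0.99 | 0.82-0.96 |
| 10 years | 0.98-1.00 | 0.92-1.00 |

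If person-time for non-stoppers ends at T − W, then P = E/h and the ratio is 1.00 at every T.

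**Step 2: calendar year 2014.** 1 January to 30 September is 273 days, and 90/273 = 33%. With nothing observable after 30 September 2014, the same formula with T = 273 days gives 0.67-0.71 of the true rate. Under the 365-day rule a confirmable stop must be dated by 30 September 2013, so no 2014 event can be confirmed.

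**Step 3: simulation.** Assumptions: hazard 0.35/year in year 1, then 0.08/year; annual mortality 1.5% or 25%; uniform entry; deregistration 0-8% per year; the article's minimum follow-up applied; full window required.

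| Quantity | Result |
|---|---|
| Overall 90-day rate | about 4% low (1.5% mortality) to 7% low (25%) |
| Overall 365-day rate | about 13% low (1.5% mortality) to 22% low (25%) |
| 2014 rate, no look-ahead | about 7.1 v 9.7 per 100 person-years (7.1/9.7 = 0.73) |
| 2014 rate, look-ahead at study end | 9.7 v 9.8 per 100 person-years |
| Cox HR, 25% v 1.5% mortality, no true difference, 90-day | about 0.98 |
| Same, 365-day | about 0.92-0.94 |

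The overall-rate percentages compare person-time to exit with person-time ended W earlier. Because the assumed hazard falls with time, part of that gap comes from dropping late, low-hazard person-time. Against a rate with every gap observed, the shortfall is smaller. Ending time at risk W earlier returns the hazard ratios to about 1.00.

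**The case against.** The strongest reply is that the effect on the main analysis is small, that this is an operational rule a condensed article may leave to the full protocol, and that the direction of bias is not fixed. Much of the first part stands: at five or more years of follow-up the 90-day rate is within about 4% of truth. The direction does depend on how incomplete windows are handled. Leaving the matter to the full protocol does not answer it, because the article itself states the event rule, the exit rule and the denominator, and applying them together produces the bias.

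Four stronger readings are tempting and are not supported:

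- **Every patient has a blind final 90 days.** Confirmed stoppers leave at their event. Patients exiting at a CVD diagnosis have later prescriptions, which the plan already uses to report continued use. The year-one and 5-year cuts can be verified wherever records continue.
- **Main-analysis hazard ratios for age and morbidity are spurious.** An HR near 0.94 appears in the 90-day analysis only if the one-year minimum follow-up is ignored. With it applied the HR is about 0.98. Other hazards give 0.96-0.99, and 10% v 1.5% mortality gives 0.99-1.00.
- **A third of 2014 is necessarily blind.** That holds only if nothing after 30 September 2014 is available. Last upload and study end are separate exits, so some practices may have later data; the article does not say.
- **The restart analysis is invalid.** It is descriptive. No confirmed stopper can restart in the first 90 days, and none is censored there, so the cumulative 6- and 12-month Kaplan-Meier proportions stand. The issue is the time origin: the first 6-month band holds only about 3 months in which a restart can occur.

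**Conclusion.** The point holds for patients whose prescriptions cannot be observed beyond exit, namely at death, deregistration, last upload, or study end without later data. For them the stated rules either keep unverifiable time in the denominator or create false stoppers. On the first reading the overall 90-day rate is about 4-7% low, the 365-day rate about 13-22% low (worse with higher mortality), and the 2014 rate about 30% low (27-33% across the calculations) without look-ahead. The false-stopper reading has not been sized. Main-analysis hazard ratios are little affected; those of the 365-day analysis move by 6-8% in the extreme mortality contrast. Hazards, mortality, entry pattern and deregistration are assumptions. The existence of the bias does not depend on them, but its size does. It matters most for the calendar trend, where an artefactual fall would sit at the last point.

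**What to change.** State one rule and use it for rates, Kaplan-Meier curves and Cox models alike:

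1. Time at risk ends 90 days (365 in the long-gap analysis) before the last date on which the patient's prescriptions are observable. A stop counts only if its finishing date falls before that point.
2. Where records run past the exit (CVD diagnosis, study end with a later upload, the year-one and 5-year cuts), use the later prescriptions to confirm or refute the gap and keep the person-time.
3. Apply the same rule to windows cut short by death, and say so. It assumes that stopping in those last days is not specially tied to dying.
4. If nothing after 30 September 2014 is available, end the calendar trend 90 days earlier (2 July 2014), or 365 days earlier (30 September 2013) in the long-gap analysis.
5. For restarts, state that none is possible in the first 90 days by definition, or start the clock at outcome date + 90 days.

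The cost is a few sentences, a small programming change, and up to 90 (365) days of person-time per censored patient. That is minor with about 600 000 patients, though noticeable in the 365-day analysis for patients followed for little more than two years.

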### Covariates

To describe the cohort and explore factors associated with the risk of discontinuation, we will consider the following covariates in six major groups. First, demographics will include age (<45; 45–54; 55–64; 65–74; 75–84 years), sex, ethnicity (Caucasian or not recorded, Indian, Pakistani, Bangladeshi, other Asian, Black African, Black Caribbean, Chinese, other ethnic group) and socioeconomic status as measured by the Townsend deprivation score in quintiles. Second, clinical values will include smoking status (non-smoker; ex-smoker; light smoker: <10 cigarettes/day; moderate smoker: 10–19 cigarettes/day; heavy smoker: 20+cigarettes/day; not recorded), body mass index (BMI) in kg/m^2^ (<25; 25–29.9; 30–34.9; 35+, not recorded), systolic blood pressure and cholesterol/high-density lipoprotein (HDL) ratio. Third, chronic diseases will include rheumatoid arthritis, chronic renal disease, liver disease, atrial fibrillation, treated hypertension, cancer, heart failure, diabetes and dementia. Fourth, genetic characteristics will include family history of premature coronary heart disease and diagnosis of familial hypercholesterolaemia. Fifth, other medications will include use of aspirin, use of anticoagulants and—as a proxy for comorbid conditions—the number of different types of medicines having systemic effect and associated with British National Formulary^39^ categories (in each case, at least one prescription in the last year before the entry date). Finally, only for patients in the primary prevention group, their 10-year cardiovascular risk as calculated by the QRISK2–2014 score (banded <5%; 5–9%; 10–14%; 15–19%; 20–24%; 25%+).

For clinical values, the most recently recorded value prior to or at the cohort entry will be used. Chronic diseases will be considered if they were recorded at or before the baseline. For the main analysis, we will use practice-based Townsend deprivation scores as these are available for the whole cohort. We will run an additional analysis on the subset of practices that have consented to link their data to Townsend scores at patient level.

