### Statistical analysis

All analyses will be performed separately for the subgroups with and without a diagnosis of CVD at the study entry date.

The numbers of incident users who stop statins will be reported and the rate of discontinuation will be assessed by dividing the number of incident stoppers by the number of person-years. The rates will be calculated overall and by calendar year, ethnic group, deprivation quintile, initial statin type, and baseline risk of CVD (for primary prevention group). We shall also calculate the percentages of patients who switch between different statins during the study period, considering a patient as a switcher if their type of statin (ingredient) changed during their follow-up. For patients in the primary prevention group who were diagnosed with CVD after entering the study, we shall report the percentages of patients who continued using statins after the diagnosis.

We shall report general descriptive statistics such as average duration of statin therapy before discontinuation, proportions of patients who had their last statin prescription within 6 months, 6 months to 1 year, 1–5 years or more than 5 years after their first prescription, and graphically summarise the data using Kaplan-Meier curves. As we expect different rates of discontinuation for short-term (less than 12 months between the first and the last prescription) and long-term (more than 12 months between the first and the last prescriptions) users, we shall calculate rates by term of use.

For those patients who discontinued statins and for those who did not, summary statistics will be calculated for the baseline covariates. We shall report frequencies and proportions for categorical data, and for continuous data, suggested bands as well as means (SD), medians and ranges. We shall also report the type of statin, the potency, calendar year for the baseline, cumulative duration of exposure before leaving the cohort (defined as the time interval between the first prescription and expected end date for the last prescription), and whether the patient had switched statin type during the study period. We shall calculate the survival-time function, report the descriptive statistics such as median duration, plot Kaplan-Meier curves for the covariates and compare the survivor functions for the covariates using the log-rank test.

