To explore the risks of statin discontinuation associated with the covariates, a Cox regression analysis will be undertaken. The model will include age, sex, ethnic group, deprivation quintile, calendar year at the entry to the cohort, baseline CVD risk and the type of statin prescribed at the baseline. Practices might differ in their prescription patterns, so we will account for clustering by practice. We shall calculate the adjusted HRs for baseline characteristics listed above: clinical values; chronic diseases; family history; use of other medications.

The proportional hazards assumption will be checked by using a log-log plot of survival for each variable. Variables which violate the assumption will be included into the model as a stratification factor. If clinically similar variables or categories (for smoking and ethnicity) are associated with similar risks, they will be combined. For continuous variables, recorded values will be used. For non-linear risk associations, fractional polynomials will be used if appropriate.^40^

As BMI, smoking status, systolic blood pressure and cholesterol/HDL ratio may be important patient characteristics but have non-negligible numbers of missing data, multiple imputation will be used to replace missing values.^41^ Five imputed data sets will be created, using multiple chained equations, and Rubin's rules will be used to combine effect estimates and SEs to allow for uncertainty due to imputing missing values. Calendar year; statin stopper status; log of survival time; age; years of records; potentially important characteristics; and type, dose and cumulative exposure to statins will be included in the imputation model.^42^

The main analyses will be run using the multiply imputed data. The least complete data are expected to be for cholesterol/HDL ratio, but information about this test is expected to be important for patient adherence. To ensure the robustness of our findings, we shall also run a sensitivity analysis including only patients with complete data.

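### Patients with no recorded ethnicity are pooled with Caucasian patients and never separated, so that group's stopping rate, and any contrast against it, is mixed

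*Protocol article*

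**What the plan says.** The Covariates section of the protocol article lists nine ethnic categories: "ethnicity (Caucasian or not recorded, Indian, Pakistani, Bangladeshi, other Asian, Black African, Black Caribbean, Chinese, other ethnic group". The first holds two kinds of patient, those recorded as Caucasian and those with no record. The same paragraph treats two other incompletely recorded variables differently. Smoking ends with "heavy smoker: 20+cigarettes/day; not recorded", and BMI is banded "<25; 25–29.9; 30–34.9; 35+, not recorded".

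The Statistical analysis section then names the variables to be imputed: "As BMI, smoking status, systolic blood pressure and cholesterol/HDL ratio may be important patient characteristics but have non-negligible numbers of missing data". Ethnicity is not among them.

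Ethnic group is used in three ways in that section:
- Rates: "The rates will be calculated overall and by calendar year, ethnic group, deprivation quintile, initial statin type, and baseline risk of CVD".
- Kaplan-Meier curves and log-rank tests, which are planned for the covariates in general.
- The Cox model: "The model will include age, sex, ethnic group, deprivation quintile, calendar year at the entry to the cohort".

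No ethnic reference category is stated. The only reference level named anywhere is simvastatin, for drug type (Exposure section).

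**The concern.** A stated aim is to identify patient groups more likely to stop statins, so the ethnic contrasts are results in their own right as well as adjustment terms. Placing everyone without a record in one substantive group fills in a missing value with certainty. Two things can follow. Some of the unrecorded will belong to minority groups and are misclassified. Separately, patients whose ethnicity was never recorded may differ in their contact with the practice. The outcome is itself the absence of a further prescription record, so it should not be assumed that missing ethnicity is unrelated to it. The large cohort (about 600 000 patients) reduces random error but does nothing about this.

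The other planned analyses do not repair it:
- The complete-data sensitivity analysis would, as written, keep these patients, because they hold a valid code.
- The Additional analyses and Sensitivity analyses sections do not address ethnicity coding.
- The plan allows ethnic categories to be merged when their risks prove similar. Here the merge is made in advance, so that check cannot be applied to the unrecorded.

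**Working it through.** **The plan's own figures.** The article gives no share of unrecorded ethnicity and no target for an ethnic contrast, so no stated figure on this point can be reproduced. Its sample-size figures do reproduce with the Schoenfeld formula, two-sided 1% and 90% power, equal allocation: 4 × 14.879 / (ln 0.9)² = 5361.5, rounded up to 5362, and 4 × 14.879 / (ln 0.8)² = 1195.3, rounded up to 1196. They concern statin types and serve here only as a yardstick for the size of effect the plan regards as worth detecting.

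**Inputs, all assumed:**
- h: true HR of a minority group against recorded Caucasian patients.
- u: share of the pooled group with no record, taken as 10% to 70%.
- g: hazard of the unrecorded relative to recorded Caucasian patients.
- m: share of the unrecorded who belong to minority groups, taken as 5% to 15%.

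**Formula.** The pooled group's hazard, relative to recorded Caucasian patients, is 1 + u(g − 1), so the HR seen is h / [1 + u(g − 1)]. This is a first-order approximation that ignores covariate adjustment.

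**Case A, misclassification only.** The unrecorded differ only because a share m have hazard h, so g = 1 + m(h − 1).
- h = 1.50, smallest effect (u = 0.10, m = 0.05): 1.50 / (1 + 0.10 × 0.05 × 0.50) = 1.50 / 1.0025 = 1.496.
- h = 1.50, largest effect (u = 0.70, m = 0.15): 1.50 / (1 + 0.70 × 0.15 × 0.50) = 1.50 / 1.0525 = 1.425.
- Over the same ranges, 1.25 is seen as 1.248 to 1.218, and 2.0 as 1.990 to 1.810.

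**Case B, the unrecorded stop at a different rate.** Take a true HR of 1.00.
- g = 1.25: from 1 / (1 + 0.10 × 0.25) = 0.976 to 1 / (1 + 0.70 × 0.25) = 0.851.
- g = 0.80: from 1 / (1 − 0.10 × 0.20) = 1.020 to 1 / (1 − 0.70 × 0.20) = 1.163.

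The extremes are comparable to, or somewhat larger than, the HRs of 0.9 or 1.1 that the plan sets out to detect for statin types. At u = 10% the shift is about 2%.

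**What imputation would do to the comparison group.** Take u = 0.40 and g = 1.20. The pooled hazard is 0.60 + 0.40 × 1.20 = 1.08. If 10% of the unrecorded are moved to minority groups, the remaining group has hazard (0.60 + 0.36 × 1.20) / 0.96 = 1.075. About 94% of the inflation (0.075 / 0.08) remains, because most of the unrecorded return to the Caucasian group. The minority groups would also gain imputed patients, and their hazards could move; that is not calculated here.

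**The case against.** The strongest reply is that most unrecorded patients may well be Caucasian, in which case their hazard belongs in that group and is not contamination. Under the assumption that 85% to 95% are Caucasian, imputation barely alters the comparison group, as the 1.075 against 1.08 shows. The error due to wrong labels is then Case A, which is small. This stands, and it rules out presenting Case B as the bias that imputation would remove. What it leaves is an asymmetry: the pooled group contains unrecorded patients while the eight other groups contain none, so the contrast is not like with like.

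Eligibility also weakens the practice-contact argument. Patients need at least two statin prescriptions, a year of prior records and a year of follow-up, and the Cox model adjusts for age, deprivation and calendar year of entry. This may reduce a difference linked to recording but cannot be assumed to remove it.

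A reader might go further and infer any of the following, none of which the article supports:
- That every ethnic rate is distorted. Rates are stoppers over person-years within each group. Eight of the nine come from patients with recorded ethnicity, and only the pooled group's own rate is mixed.
- That the pooled group is the declared reference. It is listed first and is probably the largest, but this is an inference.
- That ethnicity is the only variable handled this way. Chronic diseases count only if recorded, so an absent record is read as absence of disease.
- That the bias hides excess stopping in minority groups. Nothing in the article says that unrecorded patients stop more often, and with g below 1 the shift is upwards.

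**Conclusion.** The point holds as a limited one. The pooling is a coding rule that the article states, so it is not detail left to a fuller document. It differs from the handling of smoking and BMI, and no planned analysis reverses it. It affects the pooled group's own rate and any HR or log-rank comparison involving that group.

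Direction and size cannot be derived from the article. Under the assumed ranges, misclassification alone moves a true HR of 1.50 to about 1.43 to 1.50. A difference in stopping rate (g of 0.80 or 1.25, up to 70% unrecorded) could show a true HR of 1.00 as roughly 0.85 to 1.16. If few patients are unrecorded, or they stop at about the same rate as recorded Caucasian patients, the effect is negligible. The pooled coding leaves a reader unable to tell which of these applies. Overall discontinuation rates and the sample-size reasoning are unaffected, and statin-type HRs could change only through adjustment.

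**What to change.** - In the descriptive and rate tables, show patients with no recorded ethnicity as their own row, with their number and discontinuation rate.
- In the Cox model, either give them their own level or add ethnicity to the chained-equations imputation already planned, and show results both ways. The two answer different questions. A separate level compares recorded patients with recorded patients. Imputation addresses misclassification and puts unrecorded patients on both sides of each contrast.
- State the ethnic reference category.
- Keep the pooled coding only as a sensitivity analysis.

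The cost is one table row, one model level or one more imputed variable, and slightly wider intervals for the ethnic HRs. No new data are needed.

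### The secondary-prevention Cox model has no term for the type of CVD or the time since its diagnosis, and nothing replaces the risk score that drops out of it

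*Protocol article*

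**What the plan says.** Sample selection places in one group "those with CVD diagnosed at or before entering the study (taking statins for secondary prevention", with no limit on the kind of CVD or its date. Statistical analysis then states: "All analyses will be performed separately for the subgroups with and without a diagnosis of CVD at the study entry date". So the secondary-prevention model stands on its own.

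The core terms are given once for both models: "The model will include age, sex, ethnic group, deprivation quintile, calendar year at the entry to the cohort, baseline CVD risk", followed by statin type at baseline. Adjusted HRs are also planned for the clinical values, chronic diseases, family history and other medications.

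The Covariates section is a closed list: "we will consider the following covariates in six major groups". Three entries bear on cardiovascular status:

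- Third group: "chronic diseases will include rheumatoid arthritis, chronic renal disease, liver disease, atrial fibrillation, treated hypertension, cancer, heart failure, diabetes and dementia".
- Fifth group: "other medications will include use of aspirin, use of anticoagulants", together with a count of medicine types. Each is judged on prescriptions in the year before entry.
- Sixth group: "Finally, only for patients in the primary prevention group, their 10-year cardiovascular risk", measured by QRISK2-2014.

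Myocardial infarction, angina, stroke or TIA, and peripheral arterial disease do not appear, and neither does any date of CVD diagnosis.

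**The concern.** The sixth covariate group is empty for secondary prevention, yet the model statement names baseline CVD risk without limiting it to primary prevention. A patient who starts a statin days after a heart attack and one who starts ten years after a stable diagnosis differ in the model only through indirect markers.

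Two things are at stake. First, the Introduction sets out to find which kinds of patient are likelier to discontinue. Type and recency of disease are the most obvious groupings within secondary prevention, and the plan cannot report on them. This holds whether or not there is any confounding.

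Second, the Introduction also asks about trends over the years and contrasts between statins, and the sample size section powers drug comparisons at HRs of 0.9 and 0.8. If type or recency of CVD is linked both to the statin chosen and to stopping, part of a drug HR would reflect the indication. If the mix of CVD among new users shifts over the years, part of a calendar-year HR would reflect case mix.

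**Working it through.** **1. What each model contains.**

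| Item | Primary prevention | Secondary prevention |
|---|---|---|
| Baseline CVD risk (QRISK2) | defined, six bands | not defined |
| Type of CVD | not applicable | not listed |
| Time since CVD diagnosis | not applicable | not listed |
| Heart failure, atrial fibrillation, aspirin, anticoagulants, number of medicines | listed | listed |

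The last row gives partial information only. Heart failure and atrial fibrillation do not identify the qualifying diagnosis. The medication markers look back over the year before entry. A patient who starts aspirin and a statin together after a first event may have no aspirin in that window, while a patient with long-standing CVD may have it. As a marker of recency, aspirin could point the wrong way.

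**2. Size of the group.** From the sample size section: 600 000 × 1/4 = 150 000.

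**3. The effect sizes the plan aims to detect.** Events needed with 1:1 allocation, two-sided 1% level and 90% power (Schoenfeld): D = 4(2.576 + 1.282)² / (ln HR)².

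- HR 0.9: 59.52 / 0.01110 = 5362, the plan's figure.
- HR 0.8: 59.52 / 0.04979, rounded up = 1196, the plan's figure.

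The point does not depend on these figures. They show that drug HRs as close to 1 as 0.9 are meant to be interpreted.

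**4. How large a spurious HR could be.** The documents give none of the inputs for this step, so all are assumptions. Let h be the HR for stopping linked to an omitted CVD feature (say, a recent event), and p1 and p0 its prevalence on the comparator statin and on simvastatin. With no true drug difference, the observed HR is approximately

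[p1(h − 1) + 1] / [p0(h − 1) + 1].

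- Balanced, p1 = p0: 1.00 for any h.
- p1 = 0.5, p0 = 0.2, h = 0.7: 0.85 / 0.94 = 0.904.
- Imbalance reversed, p1 = 0.2, p0 = 0.5, h = 0.7: 0.94 / 0.85 = 1.106.

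Range with p0 = 0.2:

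| h | p1 = 0.2 | p1 = 0.3 | p1 = 0.4 | p1 = 0.5 | p1 = 0.6 |
|---|---|---|---|---|---|
| 0.9 | 1.00 | 0.990 | 0.980 | 0.969 | 0.959 |
| 0.7 | 1.00 | 0.968 | 0.936 | 0.904 | 0.872 |
| 0.5 | 1.00 | 0.944 | 0.889 | 0.833 | 0.778 |

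The formula gives no credit to the partial proxies and is only approximate when stopping is common. Weak links or small imbalance give a shift of 0 to 4%. A moderate link with clear imbalance gives a shift as large as the effect the plan is powered to find.

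**The case against.** - **The aim is descriptive.** The Cox model is presented as exploring associations, and no causal drug effect is claimed. For a question about change over time, a shift in case mix is part of the answer. This stands in part: the HRs remain valid as associations, and both sets of estimates should be shown. It does not explain why two obvious predictors are missing from a study that looks for predictors.
- **The risk term simply drops out.** The model is written once for two fits, and the rates by baseline risk are expressly limited to primary prevention. That is a fair reading, and a 10-year risk score would not measure type or recency anyway. But the model statement should say so, and the secondary model is still left with no measure specific to the qualifying disease.
- **Proxies are present.** They are, and it would be wrong to say that the model knows nothing about cardiovascular status. They are indirect, for the reasons given in the check.
- **An article condenses.** The Covariates list goes down to cigarettes per day and BMI bands, so it reads as a stated choice. The Abstract mentions rates by morbidity, but the morbidities listed leave out the qualifying CVD.
- **Recency may be hard to derive.** Forming the group needs only some CVD record, and old diagnoses may be re-entered. This stands as a limit on the fix.

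A reader might go further and infer that the statin-type and calendar-year HRs are in fact confounded by indication. The documents do not support that. They give no data linking type or recency of CVD to statin choice, entry year or stopping. For calendar year, the proper term is changing case mix.

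**Conclusion.** The omission is established from the text: in secondary prevention, baseline CVD risk is undefined and unreplaced, and neither type nor recency of CVD is a covariate. The certain consequence is that stopping cannot be reported by these groups. The possible consequence is distortion of the statin-type HRs (confounding by indication) and of the calendar-year HRs (case mix).

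The size of any distortion cannot be found from the documents. It is nil if the omitted features are balanced across statins. It reaches about 0.90 under the assumed 50% v 20% prevalence and HR 0.7, with the proxies ignored. No probability of a false positive finding should be attached, because that would need further assumed inputs such as the proportion stopping. The gap should be closed before analysis. It does not invalidate the planned associations.

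**What to change.** In Covariates and Statistical analysis:

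1. State that baseline CVD risk enters the primary-prevention model only.
2. For the secondary-prevention model, add the type of CVD at entry and the time from the most recent recorded CVD diagnosis to the entry prescription, in bands (for example up to 90 days, 91–365 days, over 1 year).
3. Report discontinuation rates by both variables.
4. Show the statin-type and calendar-year HRs with and without them, so that the reader sees both the overall pattern and how much of it case mix accounts for.
5. Describe these HRs as associations.

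The cost is two derived variables and some wording. CVD records at or before entry must already be identified to form the group. The downside is some misclassification of recency where an old diagnosis is re-entered. The interval may also be mismeasured as time to first statin where earlier use precedes the 12-month look-back, so the entry prescription is not the patient's first ever.
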